**Aim 3.** Test the effects of RIWP intervention and engagement with CBOs to increase access to benefits of structural interventions (local/state relief-related policies) for Latinx and Black immigrants and refugees.

**3.1** CBO and RIWP participants will be more likely to experience direct benefits of structural policy interventions than the comparison group of randomly sampled immigrants (RS).

In addition to the primary aims, our study design allows for exploration of key *secondary* aims: a) examine mechanisms of intervention effectiveness; b) test potential moderators of impact; and c) track policy changes to obtain preliminary quantitative estimates of effects of these structural interventions on mental health, stressors, and economic precarity using propensity score matching.^9,10^ Qualitative interviews with a purposive subsample of participants and CBO staff will allow further examination of policy intervention effects, how CBOs contribute to enacting policies and helping people benefit from them, and contexts of RIWP implementation.

Rigorous Experimental Research Design

This mixed methods study will employ a longitudinal randomized waitlist control group design with 5 data collection points over 32 months with 1240 Latinx immigrants and 60 African refugees (see Figure 2). Of this total number, 1000 Latinx immigrants will be a random sample comparison group (we have increased the random sample comparison group from 300 to 1000 participants because we have been advised by our survey consultants/subcontractors that we need to start with 1000 survey participants in the random sample in order to ensure we have an adequate sample size by the 5^th^ timepoint, which is 32 months later). The other 240 Latinx and the 60 African refugees will be recruited through 5 CBO partners, and, in addition to the same timepoints of survey data collection, will be randomly assigned after the first timepoint to the 16-week RIWP intervention or a treatment-as-usual (TAU) waitlist control group (who will receive the RIWP intervention in Year 3). A purposive subsample of 36 participants [15 from RIWP intervention group (12 Latinx and 3 African), 15 from TAU group (12 Latinx and 3 African) and 6 from RS (random sample comparison group)] will complete qualitative interviews at all 5 timepoints.

[figure not shown]

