**Aim 2**. Test the effects of engagement with CBOs to reduce adverse consequences of the COVID-19 pandemic. Analyses will use both the CBO sample and the random sample of Latinx respondents from across the state. The primary predictor is whether the participant is recruited through the CBO or random community sample. Our analyses test whether respondents recruited from CBOs differ from those in the random sample in outcomes and whether those differences change over time. While the comparison sample is a random probability sample of Latinx immigrants, the CBO sample consists of respondents already connected to a CBO, thus we propose to use propensity score matching^101,102^ with data collected at baseline to match those in each sample. The matched samples used for data analysis will adjust for systematic differences between the random sample and those who engage with CBOs. Our baseline measures have been chosen to include variables which are likely to predict an individual’s exposure to a CBO. To examine the effects of engagement with CBOs, we propose a longitudinal model with random effects for both individuals and CBOs. The model will also adjust for effects of the RIWP intervention observed in Aim 1. We note that the adjustment for clustering within CBOs only takes place for those in the CBO arm; in the comparison arm where there is no nesting, these random effects are assumed to be zero.^103,104^ In mixed notation the model for psychological distress is:

${Distress}_{tij}= B_{000}+{\gamma_{001}\left( CBO \right)+{B_{100}\left( Time \right)+\gamma_{101}\left( CBO*Time \right)\boldsymbol{+B}}_{\boldsymbol{010}}\left( \boldsymbol{covariates} \right)+{B_{020}\left( RIWP \right)+B_{030}\left( RIWP*Time \right)+ u_{00j}+u}_{10j}\left( Time \right)+r_{0ij}+r_{1ij}(Time)+ e}_{tij}$

where CBO is an indicator indicating whether individual *i* is engaged with the CBO, Time is a variable indicating the time of observation in years. For this analysis, Time will be centered around the midpoint of the study because engagement with the CBO is ongoing from before the study began. Thus, our aim is answered by Y_001_ which is the difference in mean levels of distress, adjusted for covariates, between those who experience the CBO and those in the random sample and by Y_101_ which is the difference in slopes over time between those who experience the CBO and those in the random sample.

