**Power.** Power estimates were obtained using a simplified pre/post design which results in conservative estimates because it does not consider the multiple assessments. Based on preliminary analyses from similar samples^42^ we assume that the correlation over-time between the outcome at baseline and posttest will be .68. We also assume that attrition in the CBO sample will be 10% based on prior RIWP research,^40^ but we allow for attrition of 30% in the random sample of Latinx immigrants, which is an appropriate attrition expectation that has limited bias in means.^111^ Finally, based on the previous trial of RIWP, observed effect sizes for significant effects were small to moderate (ranging from Cohen’s D of .30 to .45),^42^ thus our objective was to determine the power for an effect size of .3 or more. For **Aim 1,** simulations adjusting for baseline values on the outcome estimate **power to be .91** to detect an effect size of .3. For **Aims 2 and 3**, there is not an established analytic approach to power and so we used statistical simulations (conducted in R, with analyses run using LME for the continuous outcome and GLMER for the binary outcome). These analyses assumed random effects for CBO and ICCs of .03 based on previous literature examining outcomes clustered within neighborhoods.^112–114^ For the **Aim 2** simulations, data were generated according to an ANCOVA model and appropriate type II error control was examined by running simulations with an effect size of 0. Across 1000 simulations, we estimate that power to detect an effect size of .30 is **.92**. For **Aim 3**, power was estimated for a binary outcome with probability of an individual in the comparison group receiving state level interventions of .2, and the level 2 variance was .10, which is approximately equal to an ICC of .03. We estimated power to detect an odds ratio of 2 for the effect of CBOs on receiving state level of interventions as **.82**. Last, power estimates were obtained for secondary aims using a simple ANCOVA formula in G*Power.^115,116^ For **secondary aim a,** power was **.90** for an effect size of .3, with power estimates ranging from .70 (d = .28) to .95 (d = .36). For **secondary aim b**, power was **.87**, with power estimates ranging from .70 (d = .24) to .95 (d =.33). For **secondary aim c,** estimates displayed power of **.80**, with effect size of .23, with power estimates ranging from .70 (d = .19) to .90 (d = .28). Thus, the study has strong power to detect the hypothesized effects in Aims 1 and 2, and moderate power to detect effects for Aim 3. Secondary aims also have moderate to strong power to detect effects.

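### The Aim 2 power of .92 comes from a baseline-adjusted ANCOVA and does not apply to the mid-study level contrast by which the Aim 2 model partly answers the aim

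*Protocol*

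**What the plan says.** All places are in the Protocol.

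- **Power paragraph, Data Analysis/Statistical Considerations.** The target is set by "our objective was to determine the power for an effect size of .3 or more". The inputs are that "the correlation over-time between the outcome at baseline and posttest will be .68", an ICC of .03 for CBOs, 10% attrition in the CBO sample, and for the comparison group "we allow for attrition of 30% in the random sample of Latinx immigrants". Aim 2 data were generated under an ANCOVA, and the result is "Across 1000 simulations, we estimate that power to detect an effect size of .30 is" .92. The simplified pre/post design is described as giving conservative power. On the null run it says that "appropriate type II error control was examined by running simulations with an effect size of 0".
- **Aim 2 paragraph, same section.** The aim is answered by γ001, a covariate-adjusted difference in mean level between CBO participants and the random sample (RS), and by γ101, a difference in slopes. Time is centred at the study midpoint because "engagement with the CBO is ongoing from before the study began". The model has RIWP and RIWP×Time terms: "The model will also adjust for effects of the RIWP intervention observed in Aim 1". CBO random effects apply in the CBO arm only and are zero in RS.
- **Design text under OBJECTIVES/AIMS.** RS was raised from 300 to 1000 on the survey consultants' advice: "we need to start with 1000 survey participants in the random sample in order to ensure we have an adequate sample size" at the fifth timepoint.

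**The concern.** The power figure and the model describe different contrasts. An ANCOVA asks whether the groups differ at follow-up given where they started. γ001 asks whether they differ in level at mid-study. Because CBO engagement predates T1, much of any level difference may already be present at T1, and baseline adjustment would then remove most of it: a gap of .30 that is fully present at T1 and stays constant becomes .30 × (1 − .68) = .096.

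Baseline adjustment also cuts the residual variance to about 54% of its unadjusted value, and this is what makes .92 attainable. It is not available to γ001. The RIWP terms and the small number of CBOs further limit the information on γ001.

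Aim 2 is one of three primary aims and is described as strongly powered. If that is untrue for one of its two coefficients, a null result could be misread as evidence that CBO engagement makes no difference.

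**Working it through.** **Inputs from the Protocol.** Effect .30; correlation .68; ICC .03; five CBOs; CBO sample 300 (150 RIWP, 150 TAU) with 10% attrition, giving 270 and 135 TAU; RS 1000 with 30% attrition, giving 700 (the former 300 would give 210).

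**Assumptions.** Two-sided alpha .05; equal correlation of .68 between all visits; RIWP as a fixed group indicator; no RS members lost to matching; the baseline outcome neither a covariate nor a matching variable.

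**Formula.** With outcome variance s², between-CBO variance τ and G = 5 CBOs,

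V = τ/G + (s² − τ)/n_CBO + s²/n_RS.

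Normal-reference power is Φ(.30/√V − 1.96). Small-sample power uses a noncentral t with Satterthwaite df.

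**Step 1: reproduce .92.** For an ANCOVA, s² = 1 − .68² = .5376 and τ = .03 × .5376 = .01613.

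- 270 v 210: V = .00323 + .00193 + .00256 = .00772; .30/√V = 3.42; power .927 (a simulation gave .917).
- 135 v 700: V = .00323 + .00386 + .00077 = .00786; .30/√V = 3.39; power .923 (a simulation gave .921).

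The stated figure is reproduced, but only as a baseline-adjusted contrast with a normal reference. With Satterthwaite df the two cases give .858 and .767.

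**Step 2: the level contrast γ001.** The variance of a five-visit mean is (1 + 4 × .68)/5 = .744. With RIWP and RIWP×Time as group terms, the RIWP participants have their own level and slope, so the CBO coefficient is TAU versus RS. The Protocol does not say what the ICC is a share of, so both scales are shown for 135 v 700.

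| ICC taken as a share of | V | .30/√V | Normal reference | Satterthwaite |
|---|---|---|---|---|
| variance of the five-visit mean (τ = .0223) | .00446 + .00535 + .00106 = .01087 | 2.88 | .82 | .63 (df 4.9) |
| total variance (τ = .03) | .00600 + .00529 + .00106 = .01235 | 2.70 | .77 | .58 (df 4.8) |

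**Step 3: the full five-visit model.** Generalised least squares on the Aim 2 model, with monotone dropout to 10% and 30% and the ICC on total variance:

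| RS at start | Normal reference | t on 4 df |
|---|---|---|
| 1000 | .80 | .56 |
| 300 | .74 | .50 |

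**Step 4: sensitivity to the ICC** (RS starting at 1000). Normal reference: .93 at ICC .01, .80 at .03, .68 at .05. With t on 4 df: .73, .56 and .45.

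**Step 5: error rate.** In null simulations with the between-CBO variance estimated from five CBOs, a nominal 5% normal-reference test rejected about 7–8% of the time. A run at effect size 0 measures exactly this type I error. It carries no information on type II error.

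**The case against.** Several points on the other side have weight.

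- **The power model is declared to be simplified.** The longitudinal model is provisional, and further power analyses are promised before it is chosen. This lowers the cost of the fix. It does not correct the figure, or the description of it as conservative, on which the current claim of strong power rests.
- **Part of the shortfall depends on the df method,** which the Protocol does not fix and which may be set in an analysis plan not seen here. That is why both references are reported. Even the normal-reference values at ICC .03 are below .92.
- **TAU-only depends on how RIWP is coded,** which is not stated. Using all 270 retained CBO participants against 700 RS, the Step 2 formula gives .86 to .91 with a normal reference.
- **γ001 is covariate-adjusted and estimated on matched samples.** Covariates could reduce the variance. Matching to fewer RS members would increase it.

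Some stronger inferences are tempting but unsupported:

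- A single figure such as .62 is only one value within the range.
- That .92 shows the RIWP terms or the enlarged RS were overlooked does not follow, because 135 TAU v 700 RS under ANCOVA also gives .92.
- That going from 300 to 1000 implies a 70–79% loss needs a fifth-timepoint target of 210 to 300, and none is stated. A 30% loss leaving 700 also fits the text.
- The five CBOs do not dominate the variance: their term is .00446/.01087 = 41% to .00600/.01235 = 49% of V for 135 v 700.
- The Protocol contains no analysis restricted to the four Latinx-serving CBOs, so a power for one does not bear on this plan.

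**Conclusion.** The point holds for γ001. The stated .92 is the power of a baseline-adjusted contrast. For the level contrast, taken as TAU versus RS with five CBOs and ICC .03, power is about .74 to .82 with a normal reference and about .50 to .63 with small-sample df. The description of the power as conservative is therefore unsupported for this coefficient.

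The range rests on the assumptions listed with the calculation and moves most with the ICC: at .01 the normal-reference power returns to about .93. Power for γ101 was not evaluated, and the Power paragraph does not say which coefficient, which CBO participants or which RS size its .92 refers to. The Aim 3 power of .82 was simulated with the same CBO structure and deserves the same recheck, but nothing here establishes that it is wrong.

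The type II label on the null run is an error of wording. The Aim 1 power is not in question: 135 v 135 under ANCOVA gives .919 against the stated .91.

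**What to change.** 1. Rerun the Aim 2 simulation from the Aim 2 model: level and slope coefficients, RIWP and RIWP×Time terms, five CBOs, Satterthwaite or Kenward-Roger df, and the RS size expected after matching and attrition.
2. Restate the power as a range over the ICC, naming the coefficient, the participants and the RS size. Remove the description as conservative for γ001.
3. Specify small-sample df for the analysis itself.
4. Code RIWP as 0 at T1 for everyone, so that the pre-randomisation data of all 300 CBO participants inform the CBO contrast.
5. Correct type II to type I in the account of the null run.
6. State the RS size and fifth-timepoint retention used for power, so that the design text and the Power paragraph agree.
7. Recheck the Aim 3 power in the same way.

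The cost is one rerun simulation, some changes of wording and probably less favourable stated powers. No extra participants or data collection are needed, and the Protocol already commits to further power analyses.

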
# OBJECTIVES/AIMS

The goal of this research is to advance the science of multilevel mental health interventions that aim to reduce the disparate, adverse mental health, behavioral, and socioeconomic consequences of the COVID-19 pandemic that are a result of complex interactions between underlying structural inequities and numerous barriers to health care. This community-based participatory research study builds on a long-standing collaboration with 5 community-based organizations (CBOs) and employs a longitudinal waitlist control group design with 5 time points over 32 months. A random probability sample of 1000 Latinx immigrants (RS) will be compared with 240 Latinx immigrants and 60 African refugees recruited through CBOs and randomly assigned to an efficacious peer advocacy and learning model (RIWP; n=150) or a treatment-as-usual waitlist control group (TAU; n=150). This innovative design allows for testing of three nested levels of intervention: 1) peer intervention model; 2) engagement with CBOs; and 3) structural interventions expected in response to the pandemic (e.g., state relief for mixed status families and expanded health insurance coverage), to which all 1300 participants would potentially be exposed. We propose three primary aims to advance mental health intervention and disparities research:

**Aim 1.** Test the effects of the RIWP intervention to reduce adverse consequences of the COVID-19 pandemic for Latinx and Black immigrants and refugees.

**1.1** *Primary Outcomes:* RIWP participants will have decreased psychological distress, daily stressors, and economic precarity as compared to randomly assigned treatment-as-usual waitlist control group (TAU).

**1.2** *Secondary Outcomes:* RIWP participants will have increased protective factors (social support, access to resources, English proficiency, cultural connectedness, health services use).

**Aim 2.** Test the effects of engagement with CBOs to reduce adverse consequences of the COVID-19 pandemic for Latinx and Black immigrants and refugees.

**2.1** *Primary Outcomes:* CBO participants will have decreased psychological distress, daily stressors, and economic precarity as compared to the comparison group of randomly sampled immigrants (RS).

**2.2** *Secondary Outcomes:* CBO participants will have increased protective factors (social support, access to resources, English proficiency, cultural connectedness, health services use).

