**Secondary Aims.** (a)   Examine mechanisms of intervention effectiveness. This secondary aim will be examined through structural equation modeling (SEM) to provide tests of mediation effects through which outcomes are impacted by hypothesized mechanisms. The same models for changes in outcomes which are developed on the random sample^110^ will be used in these analyses. These analyses assess whether differences in outcomes between treatment groups are due to changes observed in protective factors from baseline to post-intervention.^111^ Significant indirect effects are anticipated linking the RIWP intervention with lower follow-up levels of distress, stressors, and economic precarity, via pre-to post-intervention increases in protective factors. Bootstrapped standard errors^105^ will be used to derive confidence intervals for these mediated effects; standard errors will be adjusted for clustering of participants within CBOs using sandwich estimators.^106^ (b) Explore whether race/ ethnicity, biological sex, gender identity, sexual orientation, age, and SES moderate intervention impact. For this secondary aim, stratification variables will be incorporated as level 2 covariates in the models described above. Moderation will be assessed via interactions between the multiple levels of treatment and each of these moderators.^107^ (c) Track local/state policy changes to obtain preliminary estimates of effects of these structural interventions on mental health, stressors, and economic precarity using propensity score matching. This aim will evaluate the impact of receiving the structural interventions which are the outcome of Aim 3 on mental health, stressors, and economic precarity. We propose to use propensity scores, but in this case where the treatment is receiving a structural intervention. Propensity scores will be developed using baseline data to predict the probability of receiving a structural intervention. We will then assess the impact of these interventions using matched samples in random effects models. Mediation will be examined using Sobel’s test to examine whether RIWP effectiveness had an indirect effect on mental health, stressors, and economic precarity through structural interventions (local/state policy changes).^108–110^ This is a secondary aim because, while important, there is not enough information to assess power a priori.

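### Secondary-aim power: aim c contradicts the plan's own statement, the ranges for aims a and c fit no single design, and aim b's .87 is unsupported for the planned interactions

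*Protocol*

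**What the plan says.** All references are to the protocol, Data Analysis/Statistical Considerations, unless stated otherwise.

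- **Method for all three secondary aims** (Power paragraph): "power estimates were obtained for secondary aims using a simple ANCOVA formula in G*Power".
- **Aim a, mechanisms.** The Secondary Aims paragraph plans mediation tests by structural equation modelling, with bootstrapped standard errors. The Power paragraph gives .90 "for an effect size of .3, with power estimates ranging from .70 (d = .28) to .95 (d = .36").
- **Aim b, moderators.** The planned test is stated as "Moderation will be assessed via interactions between the multiple levels of treatment and each of these moderators". The power given is .87, with no effect size beside it, and a range from .70 at d = .24 to .95 at d = .33.
- **Aim c, policy effects.** The Secondary Aims paragraph ends with "This is a secondary aim because, while important, there is not enough information to assess power a priori". The Power paragraph then gives .80 at d = .23, with .70 at d = .19 and .90 at d = .28.
- **Conclusion drawn.** The closing sentence of the Power paragraph rates the power of the secondary aims as moderate to strong.

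**The concern.** One method is used for three aims whose planned tests differ: an indirect effect, an interaction, and a comparison in propensity-matched samples. Aim c has a power figure that the preceding paragraph says cannot be had. In aim a, power rises by 20 points while d rises by .02, which looks too steep for a fixed sample. In aim b, .87 for moderation stands close to the .91 stated for the Aim 1 main effect, although an interaction is usually estimated less precisely than a main effect in the same people.

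At stake is how the secondary results are read. A reader who accepts the closing sentence would take a non-significant moderation or mediation result as more informative than the design allows.

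**Working it through.** **Inputs.**
- Baseline–posttest correlation: "we assume that the correlation over-time between the outcome at baseline and posttest will be .68". Residual variance is 1 − .68² = .5376, so the adjusted SD is .733.
- CBO sample: 150 per arm (Objectives/Aims). "We also assume that attrition in the CBO sample will be 10% based on prior RIWP research", so 135 per arm and 270 in all.
- Random sample: "we allow for attrition of 30% in the random sample of Latinx immigrants", so 1000 becomes 700.
- Alpha is not stated. Two-sided .05 is assumed, with z = 1.96.

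**Reproducing the plan first.** For a two-arm ANCOVA in the CBO sample:
- SE = √(.5376 × 2/135) = .0892.
- Power at d = .30 is Φ(.30/.0892 − 1.96) = .919 (.918 by the noncentral F).
- The .91 for Aim 1 and the headline .90 for aim a both reproduce closely.
- The same design gives .878 at d = .28 (stated .70) and .980 at d = .36 (stated .95). Those two do not reproduce.

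**Do the points of each aim share a curve?** For a fixed design, power = Φ(k·d − 1.96), so k = (1.96 + z_power)/d must be the same at every point. The brackets allow ±.005 for rounding in both d and power.

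| Aim | Power at d | k |
|---|---|---|
| a | .70 at .28 | 8.87 (8.67–9.09) |
| a | .90 at .30 | 10.81 (10.54–11.09) |
| a | .95 at .36 | 10.01 (9.75–10.30) |
| b | .70 at .24 | 10.35 |
| b | .95 at .33 | 10.92 |
| c | .70 at .19 | 13.08 (12.67–13.51) |
| c | .80 at .23 | 12.18 (11.85–12.53) |
| c | .90 at .28 | 11.58 (11.28–11.89) |

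- **Aim a.** The three intervals are disjoint, and they stay inconsistent at the other alphas tried (two-sided .01, .025, .10 and .20). Anchored at .90 for d = .30 (k = 10.81), power is .857 at .28 and .973 at .36. Power .70 falls at (1.96 + .524)/10.81 = .23, and .95 at (1.96 + 1.645)/10.81 = .33.
- **Aim c.** No k lies in all three intervals at two-sided .05. Anchored at .80 for d = .23, power is .638 at .19 (stated .70) and .927 at .28 (stated .90).
- **Aim b.** The points nearly fit one curve. Anchored at .70 for d = .24, power .87 falls at d = .298, and power at .33 is .927 (stated .95). The k of 10.4 to 10.9 is close to the CBO-sample main-effect value, 1/.0892 = 11.2.

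**What an interaction would give.** Let .30 SD be the difference between two subgroup effects. Then SE = √(.5376 × Σ 1/n_cell), and the detectable difference at 80% power is (1.96 + .842) × SE.

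| Contrast and moderator | Retained per cell | SE | Power at .30 | Detectable at 80% |
|---|---|---|---|---|
| RIWP/TAU, 50/50 | 67.5 × 4 | .178 | .39 | .50 SD |
| RIWP/TAU, Latinx/African 80/20 | 108, 108, 27, 27 | .223 | .27 | .63 SD |
| CBO/random sample, 50/50 | 135, 135, 350, 350 | .105 | .815 | .29 SD |

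The 108 and 27 are 240 and 60 less 10%, split over two arms. The last row uses everyone retained, with no matching and no clustering, so it is an upper value. With 1:1 matching (270/270; the ratio is an assumption), the SE is .126 and power is .66.

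**The case against.** **Aim b.** A reader might infer that .87 demonstrably came from a main-effect formula. The protocol does not say so. It names only an ANCOVA formula, and such a routine can be applied to an interaction term. The metric matters too. If d were twice Cohen's f for the interaction term (f = .15), then λ = 270 × .15²/.5376 = 11.3 and power would be about .92. That convention implies a subgroup difference of .60 SD in a balanced layout, which the protocol does not state. The planned interactions also cover the CBO-versus-random-sample contrast, where about .82 is attainable at best. Age and SES may be continuous, and the two-group formula does not cover them. All of this stands, so .87 is unsupported rather than proven wrong. The larger contrast does not help for Latinx versus African, however: the random sample is Latinx only, so that comparison exists only inside the CBO sample.

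**Aim a.** A reader might infer that .90 is too high for mediation. That has not been shown: the headline reproduces as a group difference, and no power for an indirect effect was computed. Only the range fails, and .28 may be a slip for .23, although .95 at .36 would still be off.

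**Aim c.** The three points could share a curve at a two-sided alpha of .20, but nothing in the protocol suggests that level.

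**Consequence.** Objectives/Aims already frames these aims as exploration, and nowhere does the protocol say that a null interaction will be read as an equal effect. The misreading is a risk that comes from the closing sentence; it is not a planned inference.

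**Conclusion.** The point holds in four parts, with different degrees of certainty.

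1. **Aim c:** the two paragraphs contradict each other outright. That the three figures are mutually inconsistent rests on two-sided .05. No corrected figure can be given, because the protocol states neither the share receiving a policy benefit nor the matched sample size.
2. **Aim a:** the range is impossible for one fixed design at any alpha tried. The headline .90 is sound for an ANCOVA group difference, which is not the test planned.
3. **Aim b:** .87 is unsupported for the planned interactions, and its curve resembles a main effect in the CBO sample. The .39 and .27 hold if .30 SD is a difference between subgroup effects in the RIWP/TAU contrast, with 270 retained, r = .68 and two-sided .05.
4. **Closing sentence:** its rating of the secondary aims does not follow from these figures.

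It would go too far to call every secondary-aim figure wrong or to carry the problem over to the primary aims; Aim 1's .91 reproduces. This should be corrected, but it does not touch the sample size or the primary analysis.

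**What to change.** In the Power paragraph:

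- **Aim c.** Delete all three power figures and keep the Secondary Aims statement. Deleting that statement instead would leave inconsistent figures standing.
- **Aim a.** Correct the range (about d = .23 for .70 and about d = .33 for .95 if .90 at d = .30 is kept). Say that .90 is the power of an ANCOVA group difference and not of the indirect effect.
- **Aim b.** Replace .87 with interaction power or detectable differences, stating the contrast, the moderator split, the meaning of d and the alpha. Under the assumptions above, these are .39 (50/50) and .27 (Latinx/African) for RIWP by moderator, or .50 and .63 SD at 80% power. For CBO versus random sample with a balanced moderator, the figure is at most about .82 before matching and clustering.
- **Closing sentence.** Drop the rating for the secondary aims and describe them as exploratory.

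The cost is a few sentences and a short recalculation. The stated figures become less favourable. Nothing in the design, recruitment or primary analysis changes.
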